## Abstract

**Background:**

Newborn health is a key issue in addressing the survival of children under five years old, particularly in low and middle income countries, and the evidence base for newborn health interventions continues to evolve. Over the last decade, maternal and under five-year-old mortality and morbidity rates have been successfully reduced in Cambodia, but newborn health has lagged behind. Evidence suggests that an important proportion of newborn mortality both globally and in Cambodia is attributable to infections and sepsis. While initiatives are being implemented to address some causes of newborn illness (related to pre-term birth and asphyxia), a country-level approach to reducing infections has not been formulated. The Newborn Infection Control and Care Initiative (NICCI) is a community and health facility linked intervention to improve health outcomes for newborns.

**Methods/Design:**

The present study applies a cluster randomized trial, using a stepped wedge design, to assess the impact of a package intervention on newborn health. The intervention components include addressing infection control in the perinatal period in health facilities, promoting infection prevention and control practices in health center and home environments, and improving the timeliness of referrals for newborns with suspected infections to appropriate health facilities, by linking families to the medical system through a network of community based volunteers who will make home visits to families in the first week of a newborn’s life.

**Discussion:**

The NICCI trial is designed to complement and enhance the Cambodian Ministry of Health strategies and objectives for maternal and newborn care. Results of the study will help to inform policy and the possible scale-up of newborn health interventions in the country.

**Trial registration:**

This trial was registered with Clinicaltrials.gov (identifier: NCT02271737) on 5 October 2014.

## Background

While global estimates of newborn mortality have been declining, it remains an important public health problem in low income countries, particularly in settings where under five-year-old and maternal mortality rates have decreased more rapidly [1, 2]. It is estimated that up to 40 % of global under five-year-old mortality occurs in the newborn period (during the first 28 days after birth) [3]. In Cambodia, maternal and under five-year-old mortality rates have been significantly reduced over the last 10 years, falling from 472 per 100,000 live births in 2005 to 206 per 100,000 live births in 2010, and 83 per 1,000 live births in 2005 to 54 per 1,000 live births in 2010, respectively. Newborn mortality, however, has been more difficult to address at 28 per 1,000 live births and 27 per 1,000 live births in 2005 and 2010 [4, 5].

In order to address the continued newborn mortality burden, the Cambodian Ministry of Health (MoH), under the guidance of the Prime Minister, resolved to redouble efforts to achieve significant progress in reducing newborn mortality at its Annual Congress in 2011. Attendees at the Annual Health Congress, including the United States Agency for International Development (USAID), the National Reproductive Health Program, and key non-governmental organizations (NGOs) and United Nations partners were called upon and agreed to work with the MoH in reducing high newborn and child mortality rates in Cambodia. As yet, however, there has been no agreed national strategy on how best to achieve the called-for reductions.

The Royal Government of Cambodia prioritized maternal mortality reduction through a fast track initiative, and is committed to improving maternal and child health [6]. While this policy proposes systemic and programmatic improvements directed at the prevention of maternal mortality, it lacks specific strategies for newborn survival in the postnatal period. The persistently high rate of neonatal mortality in Cambodia may be due, at least in part, to the targeting of interventions at the antenatal, delivery, and immediate postpartum periods in the health care facility. Care coordination between the health facility and the community has not been strengthened sufficiently, and infants often receive either inadequate follow-up during the transition from birth facility to community, or no follow-up at all. A total of 63.6 % of mothers reported receiving a postnatal visit within the first four hours after birth, but only 7.4 % were seen by a health care professional four to 23 hours post-delivery, and only 11.3 % were seen in the crucial period of one to two days after the baby was born [5].

A number of trials have been conducted in sub-Saharan Africa and South Asia [7–10] illustrating the utility of home visits by community volunteers to reduce newborn mortality. A recent Cochrane review, on the subject of community based intervention packages for reducing maternal and neonatal morbidity and mortality and improving neonatal outcomes, found encouraging evidence of the value of integrating facility care with newborn care in community settings through a range of interventions delivered via community health workers [11]. While community-level care is important, even greater impact may be achieved by simultaneously improving treatment of ill newborns at the community and health facility level, particularly in cases of infection and sepsis [12]. Improving service delivery for newborns through hygienic facilities and facilitated referral may impact the Cambodian development target for child health.

Currently, clinics follow the Safe Motherhood Clinical Protocol (SMCP) for health centers, which provides standard guidelines for health centers on maternal and newborn care. The SMCP instructs midwives on signs of maternal infection that should be monitored: fever, discharge, and upper or lower urinary tract infections.

The Management of Selected Newborn Problems section of the SMCP provides guidance to the health center staff for providing education to mothers on identifying symptoms and conditions that should prompt the family to bring their newborn to the health facility. However, the protocol is not clear on how to treat some of the noted conditions. For example, parents are advised that convulsions are a danger sign indicating the infant should be referred to the health facility, but there is no guidance for medical providers on how to manage the newborn with convulsions upon arriving at the health facility. The SMCP provides guidance on teaching mothers how to treat some health issues at home, such as treating local infection using gentian violet for skin infection or 1 % tetracycline eye ointment for eye infection, but there is no instruction on what steps to take if there is no improvement [13]. As a result, clinic staff are not properly trained to treat the child, and families may be sent home or resort to the private sector. If home treatment does not work, the newborn is then referred to the provincial or national hospital for a higher level of care.

Formative research conducted in the setting for this study, Takeo province, revealed gaps in essential newborn care practices [14], and barriers to infection prevention and control [15]. The data from that formative research guided the intervention design, and contributed to identifying behavioral and logistical targets for the intervention package components.

### Setting

Takeo is one of 25 provinces in Cambodia, located in southern part of the country, with a population of 843,931 (Fig. 1). The province is subdivided into 10 political administrative districts and 100 communes. As with other provinces, the health system includes a provincial hospital and one-referral hospital for each operational district. In Takeo, there are five operational districts (health administrative districts), 73 health centers, three primary referral hospitals, and one secondary referral hospital [16]. In each village there are at least two Village Health Support Groups (VHSGs), which are made up of community health volunteers.

**Fig. 1 Fig1:**
[figure not shown]
Map showing location of Takeo Province in Cambodia. The study will be conducted in Takeo Province (highlighted in red), which is south of the capital city, Phnom Penh, bordering Vietnam

## Methods/Design

The Newborn Infection Control and Care Initiative (NICCI) is a community and health facility linked intervention to improve health outcomes for newborns. The trial aims to develop and implement a package intervention at the health center, community, and household levels, designed to improve care practices and care-seeking for newborns. The intervention will be evaluated through a cluster randomized trial. The findings of the study will be used to inform policy and strategies affecting newborns in Cambodia.

### Specific objectives

The specific objectives of this trial are as follows:To improve infection control behavior of staff in selected health centers, and train staff on infection control messages to be delivered to pregnant and newly delivered women.To improve referral of sick newborns by VHSG volunteers and health center staff through: telephone-based care coordination between health center staff and VHSG volunteers when newborns are sent home with mothers; increased recognition of danger signs; and shorter time between recognition of danger signs and care-seeking at an appropriate health facility.To improve knowledge of newborn danger signs and appropriate referral for sick newborns by mothers and families of newborn infants.To diagnose the causes of sepsis among infants with possible sepsis who are hospitalized at Takeo Provincial Hospital, through blood cultures and appropriate antibiotic therapy.

### Hypotheses

Our first hypothesis is that by delivering a coordinated intervention that combines improved education for health center midwives, village health care workers, and mothers of newborns, along with improved care coordination via an increased number of interactions (points of contact) between mothers and health care personnel, we will see improved knowledge of both infection prevention methods and newborn danger signs among mothers and health care workers, more rapid case detection of significant newborn illnesses, and more rapid and appropriate referral of ill newborns in the intervention areas, as compared with those not yet receiving the intervention. We also hypothesize that the common causes of newborn sepsis in Cambodia are different from those reported in other regional settings. We will evaluate the causes of newborn sepsis in infants referred to Takeo Provincial Hospital.

### Outcomes

#### Primary outcomes

The primary outcomes for the study are as follows:Percentage of mothers who know at least three danger signs;Percentage of VHSG volunteers who know six danger signs;Percentage of families who seek care from an appropriate facility;Decreased time between onset of suspected danger signs and referral to appropriate facility;Improved infection prevention behaviors by family, as measured by the proportion of hand washing with soap at key events, calculated as a composite score from the percentage of mothers or caretakers reporting hand washing at the following key events: after going to toilet, before touching newborn, before eating, and after cleaning baby’s bottom;Improved infection prevention and control behavior among health center staff, as measured by the proportion of appropriate hand washing with soap or disinfectant at key points in provision of care to mothers and newborns, calculated as a composite score from: percentage of health center staff reporting hand washing: before patient contact (when they examine mother and newborn), before and after aseptic procedure, after exposure to blood or body fluids, after patient contact (after removing gloves), and after touching patient surroundings.

#### Secondary outcomes (intermediate outcomes)

The secondary outcomes for the study are as follows:Percentage of newborns visited at least once by VHSG volunteers on or before day seven of life,Percentage of newborns visited at least twice by VHSG volunteers or before day seven of life,Percentage of VHSG volunteers who can deliver hygiene messages,Percentage of mothers who received messages on hygiene from health center staff,Percentage of mothers who received messages on hygiene from VHSG volunteers,Percentage of mothers who received messages on care-seeking from VHSG volunteers,Percentage of health center staff who know six danger signs, andPercentage of health center staff who recall hygiene messages.

#### Exploratory outcomes

The exploratory outcomes for the study are as follows: all-cause newborn mortality, and cause- and age-specific newborn mortality. While our study may not be sufficiently powered to show reductions in mortality, we anticipate that if the hypothesis above is sustained with larger populations, the intervention will be associated with a reduction in all-cause mortality, and more specifically, in infection-associated mortality.

### Process evaluation

The intervention is likely to reduce the risk of infection, and improve the timeliness of care-seeking if infection does occur. By doing so, neonatal morbidity and mortality would likely be reduced. As this is a package intervention, the indicators chosen will evaluate different components to facilitate understanding of how components related to any change in intervention versus comparison groups. Indicators have been selected which best represent the pathways to determining the effect of the intervention, and additional process indicators will further contribute to understanding the intervention effects and why the intervention was or was not effective. The indicators chosen have also been used in several other comparable studies of package interventions aimed at improving newborn survival at a community level. Reach, coverage and/or delivery exposure, and fidelity will be evaluated during the process evaluation.

#### Primary outcomes

The primary outcomes of the process evaluation are as follows:Percentage of newborns visited by a VHSG volunteer within 24 hours of arriving home,Percentage of newborns visited by a VHSG volunteer on day three of life,Percentage of newborns visited by a VHSG volunteer on day seven of life,Number of VHSG volunteers trained,Number of health center staff trained,Presence of training materials in VHSG equipment, andPresence of training materials in health centers.

### Trial design

The health center functions as the unit of allocation, with health centers randomized to an intervention start date using a stepped wedge design. The design is principally a matched one, with before and after comparisons for each unit of randomization. On the hypothesis that 16 health centers are recruited, one health center will be assigned to start each month, and randomization will be stratified in order to ensure balance across time points. In this design, all clusters (health centers) receive the intervention in due course (unidirectional crossover) and, in particular, the intervention is never removed once it has been implemented, which allows convenience and alleviates ethical concerns. All cases will be used in the primary analysis, constituting an intent-to-treat approach. Full study enrollment will be completed at 16 months and duration of participation in the intervention will vary based on randomization assignment, with all clusters enrolled with a unidirectional approach and participating for the last six months of the trial.

All health centers in the trial will be included in the intervention, but will be randomized to one of 16 start dates. The center-level intervention will be implemented one stage at a time, progressively over the study period, until all centers have received the intervention. In addition to center level, patient-level data will also be collected. Thus the analysis is divided into center level and patient level, with the patient-level analysis as the primary outcome. All live births occurring in the study area will be eligible, and pregnant women in the last trimester will be recruited from health center catchment areas using the stepped wedge design, where each area will serve initially as control and later as intervention. The study will enroll a target sample size of 1,957 recently delivered women.

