### Sample size and power calculation(s)

Using all-cause newborn mortality as the exploratory outcome and a stepped wedge design for cluster randomized trials, we would require a total sample size of 1,957, based on 80 % power, a 5 % significance level, and a 10 % rate of loss-to-follow-up, to detect a 20 % reduction in neonatal mortality with a baseline of up to 40 deaths per 1,000 live births at the provincial level. For this study, health centers with an expected minimum of 20 births per month will be included, resulting in a study population of at least 320 per month, or 5,540 participants over one year and five months. This will allow us to meet more than 80 % power of the study primary objectives. Secondary analyses will examine the impact through process indicators based on a smaller sample. Other intervention phase outcomes with higher baseline rates than all-cause mortality (incidence of newborns with specific danger signs and proportion of newborns with danger signs referred to an appropriate facility) are hypothesized to demonstrate 20 % or greater improved outcome in the intervention group, but the lack of reliable baseline data on these does not allow us to use them for power calculations.

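### The protocol does not say whether about 1,957 women or all eligible births will be enrolled, and its figure of 5,540 participants should be at least 5,440

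*Protocol article*

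**What the plan says.** Two sections of the protocol article bear on how many women enter the trial.

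- **Trial design** states the enrolment total: "The study will enroll a target sample size of 1,957 recently delivered women". It makes eligibility universal ("All live births occurring in the study area will be eligible") and recruits from catchment areas "where each area will serve initially as control and later as intervention". On timing it says "On the hypothesis that 16 health centers are recruited, one health center will be assigned to start each month" and "Full study enrollment will be completed at 16 months", and it adds that all clusters take part for the closing six months.
- **Sample size and power calculation(s)** uses the same number as a requirement ("we would require a total sample size of 1,957", for 80 % power with 10 % loss to follow-up). It then describes expected accrual: it takes centres that expect 20 or more births a month, and gives the yield as "resulting in a study population of at least 320 per month, or 5,540 participants over one year and five months". The next sentence says that this population gives more than 80 % power for the primary objectives.

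Neither section gives a sampling fraction, and neither says that recruitment stops at a total.

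**The concern.** The number 1,957 appears once as a requirement and once as what the study will enrol. The number 5,540 is described as participants, not as births available, and it carries the power claim. A reader cannot tell whether the trial is an all-births study of about 5,440 women or a study of roughly a third of births. If enrolment is 1,957, the sentence claiming more than 80 % power describes a different trial from the one being run.

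This matters more in a stepped wedge than in a parallel trial, because the information depends on how participants are spread over centres and months as well as on their total. A total given without its spread does not define the design. The larger figure also fails a direct multiplication of its own inputs.

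**Working it through.** **Inputs** (all from the protocol article): 16 centres, one starting each month (Trial design); at least 20 births per centre per month, at least 320 per month overall, 17 months, 10 % loss (Sample size section); 1,957 (both sections).

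**1. The stated 5,540.**
- Monthly accrual: 16 × 20 = 320, as stated.
- Over 17 months: 320 × 17 = 5,440, not 5,540. The difference is 100, and 100/5,540 = 1.8 %.
- To reach 5,540 would take 5,540/320 = 17.3 months, or 5,540/17 = 325.9 births per month.
- After 10 % loss: 5,440 × 0.9 = 4,896.
- Both 20 and 320 are given as minima, so 5,440 is a floor and not a forecast.

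**2. The gap between the totals.**
- 5,540/1,957 = 2.8, and 1,957/5,440 = 36 % of the minimum expected births.
- Spread evenly over 17 months: 1,957/(16 × 17) = 7.2 women per centre-month, against at least 20 births. Over 16 months: 1,957/(16 × 16) = 7.6.

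**3. What 1,957 would mean as a stopping total.** Assume that every birth is enrolled at 320 per month and that recruitment closes at 1,957. Then 1,957/320 = 6.1 months. Six full months give 1,920 women, and the last 37 fall in month 7.

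| | First month all control | First centre starts in month 1 |
|---|---|---|
| Control, months 1–6 | 320+300+280+260+240+220 = 1,620 | 300+280+260+240+220+200 = 1,500 |
| Intervention, months 1–6 | 0+20+40+60+80+100 = 300 | 20+40+60+80+100+120 = 420 |
| Last 37, control / intervention | 37 × 10/16 = 23 / 14 | 37 × 9/16 = 21 / 16 |
| Total, control / intervention | 1,643 / 314 (84:16) | 1,521 / 436 (78:22) |
| Centres never seen under intervention | 10 of 16 | 9 of 16 |

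Either column contradicts the Trial design statement that each area contributes first as control and later as intervention. So 1,957 and all-births enrolment cannot both be taken literally.

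**4. The duration behind the total.** The 17 months are not clearly the trial's length. Sixteen monthly starts fit 17 months if one all-control month comes first. But if the last centre starts in month 16 and all centres then take part for six months, counting month 16 as the first, the end falls in month 21, and 320 × 21 = 6,720. If full enrolment at 16 months refers to women, the total is 320 × 16 = 5,120. The sections do not settle this.

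**The case against.** The strongest reply is that the two figures have different roles. The Sample size section gives 1,957 as a requirement and 5,540 as the population expected to result, and recruiting more than the minimum is no contradiction. That is right as far as it goes: a reader might infer that the totals are incompatible, and the Sample size section alone does not support this. The reply does not cover Trial design, which states 1,957 as what will be enrolled. Nor can 1,957 be the smaller sample mentioned for the secondary process analyses, since it is the mortality calculation.

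A reader might also infer that the trial will close in month 7 with an 84:16 split. The document does not support that either. Nothing says recruitment stops at 1,957. Both-phase recruitment, the roll-out to every centre and the 16-month enrolment statement (which may refer to clusters) all point the other way.

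Two further replies have weight. The slip of 100 is small, its inputs are minima, and no other figure in the article depends on it. And how a sub-sample would be drawn is detail that a condensed article may leave to the full protocol, so its absence is not the point here. A risk that field staff would select women differently by phase would likewise be inference, since the article describes neither blinding nor selection by staff. What stands is that the article fixes one total in one section and rests its power claim on another.

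**Conclusion.** The point holds as an unreconciled sample size together with a multiplication error. The planned enrolment is stated as 1,957 in one place, the power claim rests on 5,540 in another, and no statement says which applies. The 5,540 should be at least 5,440 on its own inputs, a difference of 1.8 % that is minor by itself.

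The 6.1-month closure with 9 or 10 centres unobserved is conditional on enrolling every birth and stopping at 1,957. It shows why 1,957 cannot serve as a stopping total; it is not a prediction of what the trial will do. The 5,440 rests on 16 centres, exactly 20 births per centre-month and 17 months, and the last of these is itself unsettled. Whether 1,957 follows from the mortality assumptions is a separate question, and nothing here depends on it.

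**What to change.** State one enrolment rule in both sections:

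- Enrol eligible births in all 16 centres in every month to a fixed end date.
- Label 1,957 as the calculated requirement and say that it is not a stopping point. It should not simply be replaced by 5,440, because it is a power requirement and not an accrual forecast.
- Correct 5,540 to at least 5,440 (about 4,900 after 10 % loss), or correct the inputs that produced it.
- Reconcile the 17 months with the 16 monthly starts, the 16-month enrolment statement and the closing six months, then recompute the total from the agreed duration.

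If only about 1,957 women can be followed, set an equal quota per centre-month, filled consecutively, and base the power statement on 1,957 instead of 5,540. The quota is about 7; exactly 7 over 17 months gives 7 × 16 × 17 = 1,904, so a few centre-months would need 8.

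**Cost.** If all births are already being enrolled, this is a change of wording. If 1,957 is the working target, enrolling all births adds 5,440 − 1,957 = 3,483 women. With the three interviews each in Data collection (third trimester, day 14, day 29), that is 3,483 × 3 = 10,449 more interviews. The quota avoids that workload but lowers precision. Trial status reports that recruitment has begun, so the amended text should also record the rule used so far.
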